### Sample size calculation

A mean difference of 3 mmHg and a standard deviation of 5 mmHg were considered relevant. Considering a statistical power of 80% and a 95% significance, the sample size was calculated as 45 eyes total.

The values considered for this calculation were obtained based on the results of previous goniotomy-like studies [11–23]. Since there were no studies designed to evaluate BANG, the results of studies evaluating the Kahook Dual Blade (KDB) (New World Medical, Rancho Cucamonga, USA) were considered.

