## Background

Glaucoma is the leading cause of irreversible blindness worldwide, affecting over 76 million people nowadays and 40 million more in the years to come [1]. Intraocular pressure (IOP) is the main risk factor related to glaucoma progression [2]. IOP can be controlled through the use of topical medications, laser, or surgery [3–5]. Filtering surgery, such as trabeculectomy, and glaucoma drainage device implantation are effective in reducing IOP, but may lead to severe intra- and postoperative complications [6, 7].

Minimally invasive glaucoma surgery (MIGS) emerges as a new class of surgeries, which may result in adequate IOP reduction, although still inferior to filtering procedures, with a high safety profile [8, 9]. MIGS can be divided into four types depending on the pathway activated by each one: suprachoroidal, subconjunctival, ciliary body, and Schlemm’s canal [8, 9].

Schlemm’s canal MIGS lowers the IOP by reducing the trabecular resistance to aqueous humor outflow through Schlemm’s canal and collector channels [10]. This can be achieved by a trabecular bypass, Schlemm’s canal dilation, or trabeculotomy. Bent Ab interno Needle Goniotomy (BANG) and Gonioscopy-Assisted Transluminal Trabeculotomy (GATT) [11] are two low-cost MIGS procedures that communicate the anterior chamber to Schlemm’s canal.

Most of the available publications on MIGS are either case series or retrospective studies, with different study protocols [11–23]. Moreover, these studies frequently include a variety of types of glaucoma, and cataract extraction is often combined with the MIGS procedure. Finally, none of these studies included the washout of antiglaucoma medications to verify the real IOP effect of the procedure [11–23]. The medication confounding factor prevents an objective interpretation and comparison of the postoperative results. The aim of this manuscript is to describe a randomized clinical trial (RCT) protocol to compare the long-term IOP-lowering effect and adverse effect profile of BANG and GATT in eyes with primary open-angle glaucoma.

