### Statistical analysis plan

The normality of the data will be assessed by the Shapiro–Wilk test. Comparison of longitudinal changes in IOP or the number of medications within a group will be done by Student’s paired *t*-test or the Wilcoxon rank sum test depending on the distribution of the data. The comparison of the above-mentioned parameters between the groups will be done by a non-paired Student’s *t-*test or the Mann–Whitney-*U* test depending on the distribution of the data. Categorical variables will be compared using the chi-square or the Fisher exact test.

A Kaplan–Meier survival curve will also be used to compare the success rates of both procedures. Complete success is defined as an IOP reduction ≥ 20% from baseline under no antiglaucoma medication at the final 12-month visit. Qualified success is defined as an IOP reduction ≥ 20% from baseline with the use of medication, but no increase in medication compared to the recruitment visit. Failure is defined as an IOP reduction < 20% from baseline, the need of additional glaucoma surgery to control IOP, IOP < 5 mmHg with the evidence of hypotony maculopathy, or persistent BCVA equal or lower to light perception. The log-rank test will be used to compare the survival curves of both procedures. *P* values < 0.05 will be considered statistically significant.

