One major barrier for the wider application of MIGS in ophthalmology is the costs involved [32, 33]. Some of the MIGS aiming at Schlemm’s canal are costly, including the Trabectome (Neomedix Inc., Tustin, USA) [26], KDB [34], Hydrus (Ivantis, Inc, Irvine, USA) [35], and iStent (Glaukos Corporation, Laguna Hills, USA) [36]. This limits the utilization of such techniques in developing countries. On the other hand, BANG and GATT are low-cost MIGS. Both techniques require a surgical gonio lens and an additional suture wire or needle, which are low cost [32, 33]. In Brazil, the average cost of a 5–0 Prolene wire used in GATT is around USD 3.00, while a 25-G needle used in BANG costs around USD 0.02. On the other hand, KDB has an estimated cost of USD 400, while iStent, USD 1000. At the time, there are no prospective studies comparing BANG to other MIGS or traditional glaucoma surgeries. Because of the low cost of both procedures, the results of this study could serve as a basis for ophthalmologists of developing countries to choose the type of goniotomy-like procedure they prefer.

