### Limitations

Our study has some limitations. Although the sample size was calculated for an 80% statistical power, it is considered a small sample size (*n* = 45 eyes). Also, procedures will be done by a single surgeon, and thus the results cannot be generalized. Moreover, the follow-up will not be masked for the investigator, since gonioscopy would identify the procedure used in that patient.

In summary, our study provides a standardized protocol that could be replicated in future studies investigating various types of MIGS. This would allow comparison between different techniques in terms of efficacy, safety, and patients’ quality of life.

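### The stated sample size of 45 eyes in total gives about 50% power for the 3 mmHg target, not 80%; the protocol's inputs require 45 eyes per group

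*Protocol article*

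**What the plan says.** The Sample size calculation section gives the inputs, "A mean difference of 3 mmHg and a standard deviation of 5 mmHg were considered relevant", and then the result: "Considering a statistical power of 80% and a 95% significance, the sample size was calculated as 45 eyes total". The Limitations section repeats the claim, "Although the sample size was calculated for an 80% statistical power", and gives the sample again as n = 45 eyes.

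Other sections fix the rest of the calculation:

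- **Design (Setting):** parallel, two arms, randomised 1:1, with IOP reduction from baseline as the primary outcome.
- **Test (Statistical analysis plan):** groups are compared with a non-paired Student's t-test, or the Mann-Whitney U test if the data are not normal. The threshold is that P "values < 0.05 will be considered statistically significant".
- **Both eyes (Interventions):** a patient with two eligible eyes receives a different procedure in each. The number of such patients is not given.

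**The concern.** The article states every main input as well as the result, so the result can be checked, and it does not follow from the inputs. The number 45 is what a two-sided unpaired t-test needs in each group, yet it is reported as the total for both groups.

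If 45 really is the total, a true difference of 3 mmHg would be missed about as often as it is found. That affects how the result will be read. The Discussion expects the findings to help ophthalmologists in developing countries "to choose the type of goniotomy-like procedure they prefer". The protocol makes no equivalence claim, but a non-significant result from a trial described as having 80% power invites the reading that the procedures differ little. With 45 eyes, such a result would still be compatible with differences as large as the one the trial was planned to detect.

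**Working it through.** **Inputs**

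| Input | Value | Source |
|---|---|---|
| Difference, δ | 3 mmHg | Sample size calculation |
| Standard deviation, σ | 5 mmHg | Sample size calculation |
| Power | 80% | Sample size calculation |
| Significance level | 0.05 | Statistical analysis plan; worded as "a 95% significance" under Sample size calculation |
| Sidedness | not stated; two-sided taken, one-sided also tried | assumption |
| Allocation | 1:1, parallel | Setting |
| Between-group test | unpaired t-test | Statistical analysis plan |

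The standardised difference is 3/5 = 0.6.

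**Trying to reproduce the stated figure**

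Normal approximation, per group:

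n = 2σ²(z₀.₉₇₅ + z₀.₈₀)²/δ² = 2 × 25 × (1.960 + 0.842)²/9 = 50 × 7.849/9 = 43.6

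This gives 44 per group, 88 in total. The t-test calculation, which allows for estimating the standard deviation, gives 44.6, so 45 per group and 90 in total. Power at 45 versus 45 is 80.4%. The figure 45 is therefore reproduced exactly per group, and not as a total.

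**What 45 eyes in total provides (22 versus 23, σ = 5)**

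- Standard error of the difference: 5 × √(1/22 + 1/23) = 1.491 mmHg.
- Power for 3 mmHg, two-sided t-test: 50.3%.
- 95% confidence interval half-width: t(43) × 1.491 = 2.017 × 1.491 = 3.01 mmHg.
- Difference detectable with 80% power: 4.27 mmHg.
- Standard deviation at which 3 mmHg would have 80% power: about 3.5 mmHg.

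**Other readings of the inputs**

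| Reading | Required number | Total eyes |
|---|---|---|
| One-sided 5%, normal approximation | 35 per group | 70 |
| One-sided 5%, t-test | 35.04, so 36 per group | 72 |
| Fully paired, σ = 5 for the within-pair difference, normal approximation | 21.8, so 22 pairs | 44 |
| Fully paired, same σ, paired t-test | 23.8, so 24 pairs | 48 |

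One-sided power with 22 versus 23 eyes is 63%. Taking 5 mmHg as the standard deviation of the within-pair difference is the same as taking 5 mmHg per eye with a between-eye correlation of 0.5, because 5 × √(2 × (1 − 0.5)) = 5.

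**Sensitivity (assumed scenarios, two-sided t-test, 3 mmHg)**

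- Five eyes lost, leaving 20 versus 20: power 45.6%.
- Standard deviation 6 mmHg with 22 versus 23: power 37.4%.
- Standard deviation 7 mmHg with 22 versus 23: power 29.0%.

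The larger standard deviations are illustrative. The reason to look at them is that the planning values came from earlier goniotomy studies, and the Background says that "none of these studies included the washout of antiglaucoma medications". The spread of washed-out IOP in this trial may therefore differ from the planning value, in either direction.

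**The case against.** The strongest counter-argument is that 45 may come from a paired formula. Patients with two eligible eyes receive one procedure in each, the primary outcome is a change from baseline, and the plan uses a paired t-test for changes within a group. The sample size section does not say whether the 3 mmHg is a difference between or within groups. A paired calculation gives 22 pairs (44 eyes) by normal approximation or 24 pairs (48 eyes) by t-test, and 45 lies between them.

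Part of this stands. The document does not say how 45 was obtained, so a per-group figure mislabelled as a total is an inference from the exact match. The conclusion about power does not depend on it.

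The paired route does not rescue the 80%. It gives 44 or 48, and an odd total cannot consist only of pairs. Every patient would have to contribute both eyes, whereas the protocol only allows for that possibility. The between-group test is unpaired and would not benefit from the pairing: in simulations of 22 complete pairs analysed with the unpaired t-test, power was 49% to 50% for between-eye correlations from 0 to 0.7. A within-group formula would answer a different question from the comparison of the two procedures.

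Three smaller points are fair. The assumed standard deviations and the five lost eyes are scenarios, not features of the plan. The Limitations section does concede that the sample is small, although it keeps the 80%. Enlarging to 90 eyes would be a substantial change for a single-surgeon trial that has been recruiting since March 2022.

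**Conclusion.** The concern holds. With the protocol's own difference, standard deviation, significance level, allocation and test, 45 eyes in total give about 50% power for 3 mmHg, against the stated 80%. The 80% figure needs 45 eyes per group, or a true difference of about 4.3 mmHg with 45 in total.

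This rests on two-sided testing, a standard deviation of 5 mmHg, a 22/23 split and no losses. A one-sided test would raise power only to 63%. Losses or a larger standard deviation would lower it; a standard deviation of about 3.5 mmHg would be needed to reach 80%. Because the power claim for the primary outcome is wrong and appears in two places, it has to be corrected.

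**What to change.** Choose one of two corrections, and apply it in both the Sample size calculation and the Limitations sections.

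1. If 45 per group was intended, state 45 eyes per group and 90 in total. This doubles the stated recruitment, for one surgeon, beyond a recruitment period that the Trial status section expects to end in March 2024.
2. If recruitment stays at 45 in total, state that this gives about 50% power for a 3 mmHg difference and 80% power for 4.3 mmHg, assuming a standard deviation of 5 mmHg, and remove the 80% claim from the Limitations section. This needs no extra patients. The cost is a less favourable power statement and a change of wording, including in the registry entry if it carries the same figure (it was not available to check).

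In either case, state that the test is two-sided and replace the 95% significance wording with a 5% significance level. Under the second option, also commit to reporting the between-group difference with its 95% confidence interval, and say that a non-significant result will not be taken as evidence that the procedures are equivalent.

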### Statistical analysis plan

The normality of the data will be assessed by the Shapiro–Wilk test. Comparison of longitudinal changes in IOP or the number of medications within a group will be done by Student’s paired *t*-test or the Wilcoxon rank sum test depending on the distribution of the data. The comparison of the above-mentioned parameters between the groups will be done by a non-paired Student’s *t-*test or the Mann–Whitney-*U* test depending on the distribution of the data. Categorical variables will be compared using the chi-square or the Fisher exact test.

A Kaplan–Meier survival curve will also be used to compare the success rates of both procedures. Complete success is defined as an IOP reduction ≥ 20% from baseline under no antiglaucoma medication at the final 12-month visit. Qualified success is defined as an IOP reduction ≥ 20% from baseline with the use of medication, but no increase in medication compared to the recruitment visit. Failure is defined as an IOP reduction < 20% from baseline, the need of additional glaucoma surgery to control IOP, IOP < 5 mmHg with the evidence of hypotony maculopathy, or persistent BCVA equal or lower to light perception. The log-rank test will be used to compare the survival curves of both procedures. *P* values < 0.05 will be considered statistically significant.

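### The plan misnames the paired non-parametric test: it gives the Wilcoxon rank sum test, not the signed-rank test, for before-after changes within a group (minor)

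*Protocol article*

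**What the plan says.** The Statistical analysis plan section of the protocol article sets three rules that bear on this point.

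- Choice of branch: "The normality of the data will be assessed by the Shapiro–Wilk test", and the result decides between a parametric and a rank-based test.
- Within a group: "Comparison of longitudinal changes in IOP or the number of medications within a group" is tested by Student's paired t-test or, failing normality, "the Wilcoxon rank sum test depending on the distribution of the data".
- Between groups: "The comparison of the above-mentioned parameters between the groups will be done by a non-paired" t-test or the Mann-Whitney U test.

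The threshold is that P "values < 0.05 will be considered statistically significant". The signed-rank test is not named anywhere in the article.

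**The concern.** Each eye supplies both a baseline value and follow-up values, so change within a group is paired data. The plan recognises this by naming the paired t-test. Its rank-based alternative does not match: the rank sum test compares two independent samples and is the Mann-Whitney U test under another name. Read literally, the plan therefore assigns one independent-samples test to both a paired and an unpaired comparison.

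An analyst who follows the text would discard the pairing. One who silently runs the signed-rank test would depart from the published plan. The branch is likely to be used for the number of medications. That is a small count (at most 3 at entry, by the inclusion criteria) and so is unlikely to look normal, and reduction in medication use is a named secondary outcome. The Discussion also offers the protocol as a standard for later studies, so the wrong name could be copied.

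**Working it through.** **Which test fits which data**

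| Comparison | Data | Parametric test named | Rank test named | Matching rank test |
|---|---|---|---|---|
| Within a group, over time | Paired | Paired t | Wilcoxon rank sum | Wilcoxon signed-rank |
| Between groups | Treated as independent | Non-paired t | Mann-Whitney U | Mann-Whitney U (= rank sum) |

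Only the first row is mismatched.

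**Inputs**

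- Eyes per group: 45 in total at 1:1 (Sample size calculation; Setting) gives 22 or 23. I use 22. The plan states no figure for the within-group tests, so there is none to reproduce. Whether 45 follows from its own inputs is a separate matter on which this point does not depend.
- Alpha: 0.05, assumed two-sided.
- SD 5 mmHg and a change of 3 mmHg, i.e. 3/5 = 0.6 SD. These are borrowed from "A mean difference of 3 mmHg and a standard deviation of 5 mmHg were considered relevant"; the article does not give them as a before-after change, so their use here is an assumption.
- Correlation ρ between an eye's baseline and follow-up values: not in the article. Assumed 0 to 0.7.

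**Why the size shifts**

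With equal SDs σ and n eyes, the variance of the mean change is 2σ²(1 − ρ)/n. An independent-samples test takes it as 2σ²/n. For a test on means the true two-sided size is then about 2Φ(−1.96/√(1 − ρ)):

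- ρ = 0: 2Φ(−1.96) = 5.0%
- ρ = 0.3: 2Φ(−2.343) = 1.9%
- ρ = 0.5: 2Φ(−2.772) = 0.6%
- ρ = 0.7: 2Φ(−3.578) = 0.03%

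The rank sum test should behave much the same way, and simulation confirms it.

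**Simulation, normal data, 22 eyes, 20,000 runs**

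| ρ (assumed) | Size, rank sum | Size, signed-rank | Power at 0.6 SD, rank sum | Power at 0.6 SD, signed-rank |
|---|---|---|---|---|
| 0 | 5.0% | 5.1% | 47% | 46% |
| 0.3 | 2.1% | 4.9% | 47% | 60% |
| 0.5 | 0.8% | 5.0% | 47% | 75% |
| 0.7 | 0.1% | 5.1% | 47% | 92% |

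Results with 23 eyes are similar. If ρ were negative (−0.3), the rank sum test would instead be too liberal, at 8.3%.

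**Larger changes**

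The plan's success threshold is a fall of at least 20% from a washed-out baseline of 20 to 36 mmHg. That is 0.20 × 20 = 4 mmHg to 0.20 × 36 = 7.2 mmHg, or 0.8 to 1.44 SD if the SD is 5 mmHg. Power, rank sum against signed-rank (2,000 runs):

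- 0.8 SD, ρ = 0.5: 77% against 92%
- 1.0 SD, ρ = 0.3: 93% against 96%
- 1.0 SD, ρ = 0.5: 95% against 99%
- 1.2 SD, ρ = 0.5: 99% against 100%

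**Count data**

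Normal data would mostly go to the paired t-test under the plan's own rule, so the check was repeated for a four-level count (0 to 3, assumed cut-points, 22 pairs, 4,000 runs, 0.6 SD shift on the underlying scale):

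- ρ = 0.5: size 1.0% against 4.7%; power 42% against 64%
- ρ = 0.7: size 0.15% against 5.0%; power 42% against 82%

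The pattern is the same for the kind of data most likely to reach this branch.

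**The case against.** The strongest reply is that nobody would be misled. The plan separates paired from non-paired t-tests correctly and uses two different names for the rank tests, so two different tests were evidently meant and one was misnamed. I accept that as the likely cause. It lowers the severity, but nothing else in the article corrects the name.

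The reply also limits the size of the problem, and most of this stands. The correlation is an outside assumption, and at zero nothing is lost. The 0.6 SD change comes from the sample size inputs and is less favourable to the rank sum test than the changes the trial hopes to see in IOP; near 1 SD both tests usually detect the change. The objection that normal data would seldom reach this branch is fair, but the count simulation answers it.

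A reader might infer that the trial's P values are simply wrong. The article does not support that: the error arises only if the test is run as named, the non-parametric branch is taken and the correlation is not zero. Nor does it support an inference of false claims of benefit, because under positive correlation the error makes P values too large. Nor does it follow that the comparison of BANG with GATT is compromised: this slip does not reach the between-group tests, the log-rank test or the tests on categorical variables.

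**Conclusion.** The point holds as a minor error of wording. The named test does not fit the paired comparison to which it is assigned, and this needs no assumption to see. The practical size does rest on assumptions: 22 eyes per group, equal SDs and a correlation of 0 to 0.7. At the upper end, a nominal 5% test has a true size near 0.1%, and about half the power to detect a 0.6 SD change is lost (47% against 92%). At zero correlation, or for changes near 1 SD or more, the loss is nil or small. The consequence is confined to rank-based before-after tests within a group, chiefly for medication counts. Under positive correlation it is a loss of power.

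**What to change.** In the Statistical analysis plan section, change the rank-based test for within-group comparisons from the Wilcoxon rank sum test to the Wilcoxon signed-rank test. Leave the Mann-Whitney U test for the between-group comparison as it is. The cost is one term in the text: no change to the design, sample size, data collection or any other analysis. It should be recorded as a correction before the data are analysed, so that using the signed-rank test is not later read as a departure from the plan.

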## Methods

### Setting

This study is an ongoing parallel double-arm, single-masked RCT that includes pseudophakic primary open-angle glaucoma (POAG) eyes. The study is coordinated by the University of Campinas, São Paulo, Brazil, and patients are recruited at two centers in the country (Hospital de Clínicas da Unicamp, Campinas, São Paulo, Brazil, and Hospital Regional de Divinolândia, Divinolândia, São Paulo, Brazil). Patients’ eyes will be randomized to BANG or GATT by a sealed envelope at a 1:1 ratio. The group allocation is masked for the patient.

The primary outcome is the IOP reduction from baseline. Secondary outcomes are a reduction from baseline of medication use, adverse effects after the intervention, and functional, structural, and quality of life evaluation. Patients will be followed for at least 12 months. This article followed the SPIRIT guidelines for its elaboration [24].

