### Inclusion and exclusion criteria

The following inclusion criteria are listed: (1) eyes with POAG, defined as an open angle on gonioscopy and structural loss detected by optic coherence tomography (OCT) and/or functional loss observed with visual field examination, (2) age between 40 and 80 years, (3) visual field mean deviation ≥  − 12 dB, (4) retinal nerve fiber layer thickness (RNFLT) ≥ 60 µm, (5) previous uneventful cataract surgery with intraocular lens implantation, (6) best corrected visual acuity (BCVA) ≥ 0.1 at the Snellen chart (LogMAR = 1), (7) IOP ≥ 18 mmHg measured in two occasions with the Goldmann applanation tonometer under a maximum of 3 IOP-lowering medications, and (8) IOP between 20 and 36 mmHg after medication washout.

Exclusion criteria are defined as: (1) secondary open-angle glaucoma (uveitis, corticoid-induced, pseudoexfoliation, pigmentary and juvenile), (2) primary or secondary angle-closure glaucomas, (3) phakic eyes or cataract surgery performed less than 30 days before inclusion, (4) previous glaucoma surgery (other MIGS procedures, glaucoma drainage devices, or cyclophotocoagulation), (5) previous vitreoretinal surgery, and (6) severe corneal opacity.

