**Fig. 1 Fig1:**
[figure not shown]
Study flow chart. BANG, bent Ab interno needle goniotomy; GATT, gonioscopy-assisted transluminal trabeculotomy; IOP, intraocular pressure; RNFLT, retinal nerve fiber layer thickness; mGCL, macular ganglion cell layer; BMO-MRW, Bruch’s membrane opening – minimum rim width; MD, visual field mean deviation; ECD, endothelial cell density; NEI-VFQ-25, National Eye Institute Visual Field Function Questionnaire 25

At baseline, a complimentary evaluation will be done, including ultrasonic pachymetry and specular microscopy (Tomey EM3000, Tomey Corporation, Japan) to measure central corneal thickness and endothelial cell density, respectively; RNFLT, macular ganglion cell layer and Bruch’s membrane opening — minimum rim width measurements are obtained with OCT (Spectralis OCT, Heidelberg Engineering, Germany) for structural evaluation; 24–2 visual field tests using SITA-Fast (Humphrey Field Analyzer, Carl Zeiss Meditec AG, Germany) for functional evaluation; and quality of life assessment with the Brazilian validated version of the National Eye Institute—Visual Function Questionnaire-25 questionnaire [25].

After meeting all inclusion criteria at recruitment, patients will be invited to participate in the study. All procedures will be fully explained and an informed consent will be obtained by one of the three members of the research team. After that, patients will be asked to interrupt the use of all IOP-lowering medications and return after 30 days to measure the IOP. The IOP measured after medication washout will be considered the baseline IOP.

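### Free improvement: the between-arm IOP comparison is unadjusted and its test is picked from the data, although washed-out baseline IOP is measured in every eye

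*Protocol article*

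**What the plan says.** Under Setting, the protocol article states: "The primary outcome is the IOP reduction from baseline". Under Participant recruitment, initial procedures, and randomization, it defines the reference value: "The IOP measured after medication washout will be considered the baseline IOP". Every eye must have this value, because eligibility depends on it: "IOP between 20 and 36 mmHg after medication washout" (Inclusion and exclusion criteria).

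The Statistical analysis plan section opens with "The normality of the data will be assessed by the Shapiro–Wilk test". It then sets the within-arm analysis, "Comparison of longitudinal changes in IOP or the number of medications within a group", and turns to the arms: "The comparison of the above-mentioned parameters between the groups will be done by a non-paired" Student's t-test, or a Mann-Whitney U test, according to the distribution. No regression, ANCOVA or other use of baseline as a covariate appears. Baseline enters only through the change itself and through the 20% reduction in the success definitions.

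The Sample size calculation section plans on a difference in means: "A mean difference of 3 mmHg and a standard deviation of 5 mmHg were considered relevant". It does not say whether the 5 mmHg is the SD of the change or of a single IOP reading.

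**The concern.** A change score fixes the coefficient of baseline at 1. ANCOVA estimates that coefficient. Where the true slope of follow-up on baseline differs from 1, the change score carries avoidable variance, and part of any chance difference in baseline between the arms stays in the estimated effect. With 22 and 23 eyes per arm, such differences are not negligible.

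The second matter is which quantity is reported. The design is planned on a mean difference of 3 mmHg, but the test is chosen after the data are seen. If Shapiro-Wilk rejects, the named primary test becomes a comparison of ranks, and the plan does not say which effect measure goes with it.

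The article names both the test and the rule for choosing it, so this is not a detail left to a fuller document.

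**Working it through.** **Inputs from the protocol article.** Difference 3 mmHg, SD 5 mmHg, 80% power, alpha 0.05 (two-sided assumed), 45 eyes in total, 1:1 allocation, baseline IOP between 20 and 36 mmHg.

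**Assumed, because the document gives no value.** The 5 mmHg is the SD of change; correlation rho between baseline and follow-up 0.3 to 0.7; baseline SD 3.5 to 4.6 mmHg. The upper limit is a uniform spread over the entry window: (36 − 20)/√12 = 4.6.

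**The plan's own figure.** Per arm, 2 × (1.96 + 0.84)² × 5²/3² = 43.6, so 44 per arm and 88 in total. The stated total of 45 is not reproduced. With 22 and 23 eyes, the unadjusted two-sided t-test has 50% power. That is the starting point here; the sample size itself is a separate matter.

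**Formulas.** Let s_b and s_p be the SDs at baseline and follow-up.

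- SD of change fixed at 5: s_b² + s_p² − 2·rho·s_b·s_p = 25, so s_p = rho·s_b + √(25 − s_b²(1 − rho²)).
- ANCOVA slope: b = rho·s_p/s_b. Residual variance: s_p²(1 − rho²).
- Share of variance removed: 1 − s_p²(1 − rho²)/25, which equals (1 − b)²·s_b²/25.
- Share of a baseline imbalance that enters the change-score estimate: 1 − b in size (a negative value means in the opposite direction). With equal SDs this is 1 − rho.

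**One case in full.** For s_b = 4 and rho = 0.3: s_p = 1.2 + √(25 − 16 × 0.91) = 4.43; residual variance = 4.43² × 0.91 = 17.9; removed = 1 − 17.9/25 = 29%; residual SD = 4.23.

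**Results** (power from the t distribution, 22 and 23 eyes, 3 mmHg):

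| Baseline SD | rho | Residual SD | Variance removed | 1 − b | Power (unadjusted 50%) |
|---|---|---|---|---|---|
| 3.5 | 0.3 | 4.55 | 17% | 0.59 | 58% |
| 3.5 | 0.5 | 4.96 | 2% | 0.18 | 51% |
| 3.5 | 0.7 | 4.84 | 6% | −0.36 | 53% |
| 4.0 | 0.3 | 4.23 | 29% | 0.67 | 64% |
| 4.0 | 0.5 | 4.85 | 6% | 0.30 | 53% |
| 4.0 | 0.7 | 4.93 | 3% | −0.21 | 51% |
| 4.6 | 0.3 | 3.60 | 48% | 0.75 | 78% |
| 4.6 | 0.5 | 4.61 | 15% | 0.42 | 57% |
| 4.6 | 0.7 | 4.99 | 0.3% | −0.06 | 50% |

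**Equal SDs as a cross-check.** If baseline and follow-up SDs are equal, the residual variance is 25(1 + rho)/2. The variance removed is then 35%, 25% and 15% at rho 0.3, 0.5 and 0.7. But equal SDs require s_b = 5/√(2(1 − rho)) = 4.2, 5.0 and 6.5 mmHg. The last two exceed the 4.6 of a uniform spread over the entry window, so this range cannot be relied on.

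**Validity and the effect of the Shapiro-Wilk step.** Simulation with normal data, equal SDs, 22 and 23 eyes, 4,000 runs per setting:

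| rho | Quantity | t-test | Shapiro-Wilk rule | ANCOVA |
|---|---|---|---|---|
| 0.3 | Type I error | 4.9% | 4.9% | 5.1% |
| 0.3 | Power | 49% | 49% | 67% |
| 0.5 | Type I error | 4.8% | 4.8% | 5.1% |
| 0.5 | Power | 51% | 51% | 62% |

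**The case against.** The strongest reply is that nothing here is an error. Under randomisation the t-test on change is unbiased and holds its type I error, as the simulation shows. This stands, and it is why the point is an improvement rather than a fault in validity.

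Several stronger readings are tempting, and the document does not support them:

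- *A baseline imbalance passes in full into the result.* Only a part does: 1 − rho with equal SDs, or 1 − b more generally.
- *Adjustment is sure to save a substantial share of the variance.* It may save almost nothing. When the slope is close to 1, change score and ANCOVA nearly coincide.
- *The Shapiro-Wilk step costs power or inflates error.* With normal data it did neither. The complaint is only that one primary effect measure is not fixed.
- *A rank test can give no figure in mmHg.* The Hodges-Lehmann shift is in mmHg, and the plan does not forbid reporting a mean difference as well. What is missing is a commitment to one measure comparable with the planned mean difference.
- *Adjustment rescues the sample size.* Under the assumptions above, no case reaches 80% power.

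The document also does not say whether the reduction is absolute or a percentage. Absolute change is the natural reading, given the planning value in mmHg, but it is an inference.

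**Conclusion.** The point holds as a free improvement. The planned comparison is sound but leaves a measured prognostic value unused, and it does not settle in advance which effect measure is primary.

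On the stated assumptions, adjustment removes between about 0.3% and 48% of the error variance. Power at 45 eyes becomes roughly 50% to 78%, against 50% without adjustment. The gain is largest when the correlation is low and the baseline spread wide, and it nearly vanishes when the slope approaches 1. The direction is secure apart from the trivial loss of a degree of freedom; the size is not, because the document gives neither the correlation nor the meaning of the 5 mmHg.

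**What to change.** In the Statistical analysis plan section, name one primary between-arm analysis: an ANCOVA of day-360 washed-out IOP on arm, with washed-out baseline IOP as covariate. Report the adjusted mean difference in mmHg with its 95% CI, whatever Shapiro-Wilk shows. Keep the Mann-Whitney test as a sensitivity analysis. In the Sample size calculation section, say whether 5 mmHg is the SD of change or of a single IOP.

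The cost is a few lines of wording and one degree of freedom (42 instead of 43 for error), which changes power by less than 0.1 percentage points. No extra visit, measurement or eye is needed. How to handle patients with both eyes in the trial is a separate matter, and this change does not depend on it.
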